# Protocol Study for the Evaluation of Non-Opioid Balanced General Anaesthesia in Cardiac Surgery with Cardiopulmonary Bypass: A Randomised, Controlled, Multicentric Superiority Trial (OFACAR Study)

**DOI:** 10.3390/jcm12175473

**Published:** 2023-08-23

**Keywords:** opioid-free anaesthesia, lidocaine, opioid, general anaesthesia, outcomes, acute kidney injury, sepsis

## Abstract

Opioid-free anaesthesia (OFA) is general anaesthesia based on the use of several non-opioid molecules that aim to have an analgesic effect, decrease the sympathetic response, decrease hormonal stress, and decrease the inflammatory response during surgery. Although this approach to anaesthesia is regularly used in clinical practice, it remains a novel approach. The literature on this anaesthesia modality finds a number of positive effects on cardiac, respiratory, and cognitive function but no randomised study evaluated these effects during cardiac surgery where there is a high incidence of postoperative complications. The main aim of the study is to compare OFA vs. standard balanced opioid general anaesthesia on the incidence of postoperative complications and the length of stay in intensive care and hospital. OFACAR is a multicentric, randomised, controlled, superiority, single-blind, two parallel-arm clinical trial in patients undergoing cardiac surgery with cardiopulmonary bypass. We compared a balanced general anaesthesia without opioids (OFA group) vs. a balanced opioid general anaesthesia with sufentanil (control group). One hundred and sixty patients will be enrolled in each treatment group. The primary endpoint is a composite one which corresponds to the occurrence of at least one of the postoperative complications, defined according to European standards within 30 days after surgery. Recruitment started in September 2019, and data collection is expected to end in November 2024.

## 1. Introduction

Intraoperative administration of opioids, in combination with hypnotics and muscle relaxants, is considered a key component of balanced general anaesthesia [1]. However, the use of opioids is associated with several side effects (hypoxaemia, confusion, postoperative pain, postoperative nausea, and vomiting), which may be responsible for an increase in operative morbidity and may be a source of postoperative misuse and addiction [2]. 

Opioid-free anaesthesia (OFA) is general multimodal anaesthesia based on the use of hypnotics and non-opioid analgesics (lidocaine, ketamine, corticoid, and esmolol). OFA has been used in the past 10 years with several positive clinical effects in randomised and non-randomised studies [3,4,5,6]. The effects are better analgesia with reduced postoperative morphine consumption, better lung function, better hemodynamic stability and better postoperative cognitive function [4,6,7]. To date, no randomised trial has evaluated OFA in cardiac surgery with cardiopulmonary bypass (CPB). Only observational studies have suggested an improvement in analgesia and a decrease in some postoperative complications [6,7]. Cardiac surgery is a major surgery that most often includes an elderly population, with a high incidence of postoperative complications (up to 50%) [8]. The occurrence of these complications is the result of a complex interaction between the patient’s preoperative condition, anaesthesia, surgery and CPB. It has also been demonstrated that each molecule used in OFA protocols can individually decrease the inflammatory response to CPB and respiratory complications and improve postoperative cognitive function and operative haemodynamic stability. In addition, the absence of opioid use would avoid the side effects associated with their use. 

Thus, the hypothesis of the present study is that OFA during cardiac surgery with CPB is associated with an improvement of intraoperative haemodynamic stability, a reduction in the incidence of postoperative complications, thus a reduction in the length of stay in intensive care and hospital. The main objective of the study is to demonstrate that OFA decreases a composite score of cardiovascular complications.

## 2. Material and Methods

### 2.1. Study Design

This study is a randomised, controlled, superiority, single-blind, two parallel-arm, multicentric clinical trial in patients undergoing cardiac surgery with CPB. We will compare a balanced general anaesthesia without morphine vs. a standard balanced general anaesthesia (with opioids). This study is conducted at the tertiary university hospitals of Dijon, Besançon and Strasbourg, in France.

Only the anaesthetist and the anaesthetist nurse in charge of the patient during the surgery are aware of the allocated treatment. They are not involved in the management of the patients before and after the surgery. Neither the surgeons, the nurse, the intensivist, nor the cardiologist are informed of the allocation group to maintain blindness during their time in the ICU and the hospital stay following surgery. The patient is kept blind about the randomisation group throughout their stay. 

Information about the study protocol is given during the anaesthesia consultation by one of the investigators (between 48 h and 2 months before the cardiac surgery), and all patients give their written informed consent during the preoperative visit (baseline visit) the day before the surgery. Inclusion and non-inclusion criteria are checked before the final inclusion and randomisation. 

### 2.2. Ethics Statement 

This study was approved by an independent ethics committee (French CPP Sud Est VI), received the authorisation of the Agence Nationale de Sécurité du Médicament et des Produits de Santé and was registered on the Clinical Trial Registration (n° 2021-000066-16, NCT04886453) before the inclusion of the first patient. The first patient was included in August 2021, and the last patient follow-up is planned for May 2024.

### 2.3. Study Population

We included adult patients from Dijon University Hospital, Strasbourg University Hospital and Besançon University Hospital undergoing cardiac surgery with CPB. The inclusion and non-inclusion criteria are provided in Table 1.

### 2.4. Randomisation 

Participants are randomised to receive either opioid-free anaesthesia (interventional group: OFA) or conventional anaesthesia with sufentanil (control group). This allocation is stratified by the centre and Euroscore 2. The 1:1 ratio randomisation is performed by an investigator not in charge of the patient on the day of the cardiac surgery to avoid bias, using the CleanWeb^TM^ software (V 176.1.0, Telemedicine Technologie SAS, Boulogne Billancourt, France), and this process is controlled by an identification using a password. The compliance of the data with the inclusion and non-inclusion criteria is checked a second time at this point. The treatment allocation algorithm of the randomisation was established by the Research Methodology Support Unit (USMR) of the Dijon Bourgogne University Hospital, which also offered technical support and keeps a confidential record of the full randomisation process.

### 2.5. Study Intervention 

Institutions follow international guidelines for the maintenance and withdrawal of preoperative medications [9,10]. Anaesthesia, CPB, and postoperative management are standardised for all patients and follow usual guidelines [10,11,12]. During the surgery, only the anaesthesia protocol differs. 

#### 2.5.1. OFA Group 

At induction, all patients receive intravenous ketamine (0.5 mg kg^−1^), dexamethasone (0.1 mg kg^−1^), lidocaine (1.5 mg kg^−1^), and magnesium sulphate (30 mg kg^−1^). Anaesthesia is maintained with the Schnider model target-controlled infusions of propofol (started at an effect site concentration of 2–4 mcg mL^−1^) and continuous infusion of lidocaine (1.5 mg kg^−1^ h^−1^ until sternotomy, then 1 mg kg^−1^ h^−1^ until end of surgery). Sedation is titrated by using the bispectral index (Covidien, Boulder, CO, USA), aiming for a value between 40 and 60.

#### 2.5.2. Control Group 

In the control group, anaesthesia is induced and maintained with sufentanil with an effect site concentration started at 0.5 ng mL^−1^ and propofol with an effect site concentration started at 2–4 ng mL^−1^. Then, anaesthesia is maintained with sufentanil by using the Gepts target-controlled infusion model and propofol by using the Schnider model target-controlled infusions (started at an effect site concentration of 2–4 mcg mL^−1^). Sufentanil is stopped at the end of the procedure. Sedation is titrated based on the bispectral index (Covidien, Boulder, CO, USA), aiming for a value between 40 and 60.

For both groups, tracheal intubation is facilitated via the intravenous use of cisatracurium (0.15 mg kg^−1^) or atracurium (0.4 mg kg^−1^). Arterial hypertension (systolic arterial pressure > 140 mmHg) is treated with esmolol in case of tachycardia (heart rate > 80 bpm) or urapidil/nicardipine in case of heart rate < 80 bpm. Fluid therapy is optimised during and after the surgery according to French guidelines [12,13]. Fluid therapy optimisation is based on Stroke Volume (SV) optimisation.

Ventilation strategy consists of a lung protective strategy (tidal volume of 6 to 8 mL kg^−1^ ideal body weight, positive end-expiratory pressure of 5 to 14 cm H_2_O, and recruitment manoeuvres) before and after CPB, and in the ICU; FiO_2_ set to obtain SpO_2_ between 95 and 99%. 

#### 2.5.3. ICU Management

At the end of surgery all patients are sedated with propofol infusion, and the lungs are mechanically ventilated until haemodynamic stability and normothermia are obtained, and blood loss is considered acceptable (less than 1 mL kg^−1^ h^−1^) [14]. A specialized team (trained in the care of postoperative cardiac surgery) manage all patients. Circulatory support is guided by using institutional protocols to achieve predefined endpoints: mean arterial pressure > 65 mmHg, cardiac index > 2.2 L min^−1^ m^−2^, and urine output > 0.5 mL kg^−1^ h^−1^. Electrocardiogram, pulse oxygen saturation, and central venous blood pressure are continuously monitored. Scheduled blood tests include arterial/venous blood gas measurements on admission to the ICU and then several times a day on the request of the attending physician.

Analgesia is standardised and comprises paracetamol (15 mg kg^−1^ every 6 h) use and morphine. Morphine is initially administered intravenously via a titration of 2–3 mg to obtain a visual analogue pain scale (VAS < 3) and then via the use of a patient-controlled morphine pump. Complementary analgesia is allowed when analgesia is insufficient (VAS > 3) despite treatment with morphine (20 mg for titration or for the cumulated dose over the last 4 h) and paracetamol. Complementary analgesia comprises ketoprofen (up to 200 mg per day), and/or tramadol, and/or nefopam. Pain is assessed every 4 h. The use of locoregional analgesia (epidural analgesia, paravertebral block, serratus block, intercostal block, and interpectoral block) is prohibited.

### 2.6. Data Collection 

The data are prospectively collected in an electronic CRF (e-CRF) created with CleanWeb software by a data manager. Demographic and surgical data are collected at the baseline visit. All patient-related data are anonymously prospectively noted in the e-CRF by a clinical research associate who is blind to the group assignment. Data consists of: gender, age, weight; size; ASA score; Euroscore 2; Apfel score; comorbidities; ventricular aneurysm; preoperative left ventricular ejection fraction (%); preoperative creatinine levels; drug consumption and the type of surgery; episodes of hypertension; hypotension; bradycardia and tachycardia; CPB time; aortic clamping time; duration of anaesthesia; biological assessment at the end of the bypass surgery; electrosystolic entrainment; total dose of propofol; sufentanil; lidocaine; ketamine; heparin; and protamine; total dose of insulin; total fluid balance; transfusion of red blood cells; tranexamic acid; catecholamine use (dose, type, duration); operative diuresis; veno-arterial ECMO; and intra-aortic counter pulsation balloon. Postoperative data comprise: time to extubation; complications; SOFA score; arterial lactates; catecholamine (type, dose, duration); total dose of insulin; total dose of morphine; postoperative pain episodes at rest and cough (VAS > 3) and the number of episodes of nausea–vomiting following 48 h after extubation; standard biological; additional analgesia. On discharge from the ICU, a QoR15 questionnaire is performed by a nurse who is blind to group assignment. 

Complications are prospectively noted from the day of operation until the 60th postoperative day (POD 60). A post-surgical consultation is performed at POD 30 and POD 60. This consultation could be replaced by a telephone call at POD 60 if it does not take place, but the information collected must correspond to the patient’s condition at POD 30. A telephone call is made at POD 90 to collect the vital status. The study scheme is presented in Figure 1.

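### Section 2.6 calls the research associate who fills the e-CRF blind, yet the data that role enters include the drug totals that reveal the arm, alongside the primary-endpoint complications

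*Protocol article*

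**What the plan says.** Three statements in the protocol article bear on this point.

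- **Who records.** Section 2.6: "All patient-related data are anonymously prospectively noted in the e-CRF by a clinical research associate who is blind to the group assignment".
- **What is recorded.** The list that follows in Section 2.6 contains "total dose of propofol; sufentanil; lidocaine; ketamine; heparin; and protamine". It continues: "Postoperative data comprise: time to extubation; complications; SOFA score; arterial lactates".
- **Who knows the arm.** Section 2.1: "Only the anaesthetist and the anaesthetist nurse in charge of the patient during the surgery are aware of the allocated treatment". The same section adds: "Neither the surgeons, the nurse, the intensivist, nor the cardiologist are informed of the allocation group to maintain blindness".

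The arms are defined by drugs on that list. In the control group (Section 2.5.2), "anaesthesia is induced and maintained with sufentanil". In the OFA group (Section 2.5.1), "At induction, all patients receive intravenous ketamine", and maintenance includes a "continuous infusion of lidocaine". Section 2.6 also gives the QoR15 at ICU discharge to a nurse described as blind.

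**The concern.** A role cannot be blind to allocation while entering the totals of the drugs that define the allocation. Section 2.6 gives that role the complications as well, and under Section 2.8 any one qualifying complication within 30 days makes the patient a primary-endpoint event.

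Detection bias is what is at stake. Some Table 2 components leave room for interpretation when taken from the notes: ARDS, postoperative myocardial damage, delirium, and low urine output over 6 hours. Because one component is enough, a single borderline entry can change a patient's primary outcome. Pain and nausea counts, which feed secondary endpoints, are part of the same data set. If nothing changes, the trial will report blinded data recording that its own data list contradicts.

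**Working it through.** The plan gives no figure to reproduce on this point. The check is a comparison of the text.

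**Step 1: does the drug page reveal the arm?**

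| Field in Section 2.6 | OFA group (2.5.1) | Control group (2.5.2) |
|---|---|---|
| Sufentanil total | not part of the regimen | given at induction and maintenance |
| Ketamine total | given to all at induction | not part of the regimen |
| Lidocaine total | bolus, then infusion to the end of surgery | not part of the regimen |

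The three totals differ in pattern between the arms, so a patient treated as assigned is identified as soon as they are entered.

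**Step 2: does the same role record the outcome?** Yes, as written. Section 2.6 assigns all patient-related data to the associate and lists complications among those data. It describes no division of entry, no hidden fields, and no order in which pages are completed.

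**Step 3: is this consistent with Section 2.1?** No. If only the theatre anaesthetist and anaesthetist nurse know the arm, the associate cannot be entering these doses. If the associate does enter them, a further role knows the arm.

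**Step 4: which components are exposed?** From Table 2:

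- Little room for a transcriber: death, creatinine rise, treatment with inotropes, non-invasive ventilation or high-flow oxygen, intubation beyond 24 hours, re-intubation, stroke on CT.
- More room: ARDS by the Berlin definition, myocardial damage by the universal definition, delirium (although CAM-ICU is named as the tool), and urine output below threshold over 6 hours.

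**Step 5: how sensitive is the primary test to a recording shift?** This is an illustration on assumed shifts. Nothing in the documents supports any particular value or direction.

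Inputs: 144 evaluable patients per arm and a 60% event rate (Section 2.9.1), two-sided 5%, no true effect. The assumption is a spurious difference d in favour of OFA.

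- Standard error: √(2 × 0.60 × 0.40 / 144) = 0.0577.
- Chance of a false significant result for OFA: Φ(d / 0.0577 − 1.96).

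| Assumed d | Net patients changed, d × 144 | False result favouring OFA |
|---|---|---|
| 0 | 0 | 2.5% |
| 3 points | about 4 | 7.5% |
| 5 points | about 7 | 13.7% |
| 10 points | about 14 | about 41% |

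The last row is a bound, not a scenario to expect. The expected number of event patients per arm is 0.60 × 144 = about 86. If the shift came only from missed OFA events, about 14 of those 86 would have to lose every qualifying component.

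**The case against.** The strongest reply is that the associate transcribes and does not diagnose. Events are established at the bedside by clinicians whom Section 2.1 keeps uninformed. The theatre anaesthetist and anaesthetist nurse take no part in care before or after surgery, and a blind nurse performs the QoR15. Many Table 2 components are charted treatments or laboratory values, which a transcriber can hardly alter. This stands, and it narrows the concern considerably.

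A reader might therefore be tempted to infer too much: that outcome assessment in this trial is unblinded, or that its protection against detection bias is absent. The documents do not support that. They show only that e-CRF recording by the associate cannot be blind as described. Nor should the percentages in the working be read as the trial's actual error rate, since the shifts behind them are assumed.

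A second reply is that the article condenses a fuller protocol, in which access rights or separate entry staff may already be set out. Section 2.6 names a role and does not say that one individual completes every page. That is a fair reason not to assert that blinding fails in practice. It does not rescue the sentence, which assigns all the data to a blind role. If entry is in fact divided, the sentence is wrong. If it is not, the blinding is not real. The word stating that data are noted anonymously does not help either, because anonymity hides who the patient is, not the arm.

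A third reply is timing. Section 2.2 puts the first inclusion in August 2021 and the last follow-up in May 2024, and the article appeared in August 2023. A change of access protects only later entries. This also stands, and it is why patients already entered need separate handling.

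**Conclusion.** The point holds in a limited form. The blinding of e-CRF recording stated in Section 2.6 is incompatible with the data list in the same section, and with Section 2.1. This is a statement that cannot be true as written, not a detail left to another document.

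The conclusion rests on the article's own wording: all data, one role, described as blind, with arm-defining doses among the fields. It does not reach bedside care, diagnosis or the QoR15. Exposure is mainly in ARDS, myocardial damage, delirium and 6-hour urine output.

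The size of any bias cannot be estimated from the documents, which give neither component rates nor any information on recording error. The illustration shows only that net shifts of about four to seven patients per arm would matter if they occurred and ran in one direction. Severity: should-fix.

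**What to change.** 1. Have the intraoperative drug page completed by the anaesthetist or anaesthetist nurse, who already know the arm, under restricted e-CRF access.
2. Hide that page and the anaesthesia record from whoever records complications and other postoperative outcomes.
3. Rewrite the sentence in Section 2.6 so that it says who enters which part and which of them is blind, in agreement with Section 2.1. If entry is already divided in this way, correcting the sentence is enough.
4. For patients entered before the change, do not describe the recording as blinded. Add a sensitivity analysis of the primary endpoint limited to objectively recorded components, such as death, creatinine rise, inotrope treatment and re-intubation. State in advance that it will have fewer events and less power than the main analysis, so a non-significant result there would not by itself contradict the main one.

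The cost is a change of access rights in the existing e-CRF, a rewritten sentence and one additional analysis. The theatre team takes on a few minutes of data entry per case (my estimate; the documents give no figure). No added staff should be needed, because the people who would enter the drug page are already present and already know the arm.

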### 2.7. Objectives 

The main objective is to demonstrate the superiority of balanced general anaesthesia without opioids (OFA) over a balanced opioid anaesthesia (with sufentanil ) on the occurrence of at least one of the serious postoperative complications at day 30 following cardiac surgery with CPB. 

The secondary objectives are to compare the two strategies in terms of the occurrence of each type of serious complication within the first 30 days after surgery, morphine consumption within 48 h of extubation, the quality of postoperative analgesia during the first 48 h after surgery, the quality of post-surgical recovery at discharge from the intensive care unit, the occurrence of arrhythmia due to atrial fibrillation and/or atrial flutter, the occurrence of vasoplegic syndrome, the occurrence of postoperative infectious episodes, the time to extubation of the patient in intensive care, the occurrence of non-serious side effects associated with morphine (nausea and vomiting), the postoperative length of stay in the ICU, the total postoperative hospital stay and the mortality at POD 90.

### 2.8. Outcomes 

The primary endpoint is a composite endpoint, which comprises the occurrence of at least one of the postoperative complications, defined according to European standards (6), within 30 days after surgery, as provided in Table 2. The complications are defined according to international recommendations (ESAIC, ESICM) [15,16]. 

The secondary endpoints are the occurrence of each type of serious complication within the first 30 postoperative days: total cumulative dose of morphine (in milligrams), the number of episodes of postoperative pain (VAS > 3) at rest and on coughing within 48 h of tracheal extubation, the post-surgical recovery by questionnaire (QoR15), the number of patients with an atrial rhythm disorder (arrhythmia due to atrial fibrillation or atrial flutter), the number of patients with an infectious episode (pneumonia, urinary tract infection, surgical site infection, or bacteraemia), the time to extubation of the resuscitation patient (hours), the number of episodes of postoperative nausea and vomiting in the first 48 h after extubation, the ICU stays in days, and the hospital stay in days.

For patients included at the hospital of Dijon, an additional blood sample specimen is constituted at different times: before the surgery, at the end of the CPB, 4 h after the CPB, on the first POD, and on the second POD.

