#### 2.9.2. Data Analysis 

The main analysis will be conducted on an intention-to-treat basis and completed by a per-protocol (Supplementary Materials; flow chart diagram). The main conclusion of the trial will be on the intention-to-treat analysis only. The quantitative variables will be described by the mean ± standard deviation and the median [25–75% IQR] and qualitative variables will be described by their number (%). The characteristics of the two groups will be compared using the usual univariate test: Chi-square test or Fisher’s exact test for qualitative variables and Student’s or Wilcoxon’s test for quantitative variables, depending on the test conditions. 

Logistic regression adjusted on the stratification factors (centre and Euroscore 2) will be performed to analyse the effect of the type of anaesthesia on the rate of occurrence of postoperative complications.

The analysis of secondary endpoints will be performed using an ANOVA adjusted for stratification factors or the Wilcoxon test depending on the distribution of the variables for quantitative variables and a logistic regression adjusted for stratification factors for categorical variables. The time to extubation will be described and compared between the two groups using Kaplan–Meier curves and a log-rank test if the application conditions are met. If factors at inclusion appear unbalanced between the two groups, multivariate analyses will be performed including these factors in addition to the stratification factors. 

An intermediate analysis will be performed after the inclusion of 25% and 50% of patients. Thus, the safety of the trial (rate of serious adverse events between inclusion and POD 30), as well as the rate of occurrence of postoperative complications, will be described and analysed according to the treatment arm. These results will be submitted to the independent safety monitoring board, who will decide whether to stop the trial. The final statistical analyses will be performed using a significant level of 5%.

The intermediate analyses will use an alpha risk of 0.001 for each safety analysis of the trial, according to the method proposed by Peto–Haybittle, in order not to modify the significance level of the final main analysis. The statistical analysis is performed using SAS Software (version 9.4). 

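### The postoperative morphine endpoint leaves out tramadol, an opioid the protocol allows as rescue, so it undercounts opioid use in patients with uncontrolled pain

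*Protocol article*

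**What the plan says.** Section 2.7 (Objectives) lists "morphine consumption within 48 h of extubation" among the secondary objectives. Section 2.8 (Outcomes) turns this into "total cumulative dose of morphine (in milligrams"). No other opioid and no conversion to morphine equivalents is named.

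Section 2.5.3 (ICU Management) standardises analgesia as paracetamol and morphine, and adds a second step for pain that stays above VAS 3 "despite treatment with morphine (20 mg for titration or for the cumulated dose over the last 4 h) and paracetamol". That step reads: "Complementary analgesia comprises ketoprofen (up to 200 mg per day), and/or tramadol, and/or nefopam".

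Section 2.6 (Data Collection) lists "total dose of morphine; postoperative pain episodes at rest and cough" and, as a separate item, "standard biological; additional analgesia". Rescue drugs are therefore recorded in some form, but Section 2.8 makes them neither part of the morphine endpoint nor an endpoint of their own. A companion endpoint in Section 2.8 is "the number of episodes of postoperative pain (VAS > 3) at rest and on coughing within 48 h of tracheal extubation".

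Section 2.9.2 (Data Analysis) assigns secondary endpoints an "ANOVA adjusted for stratification factors or the Wilcoxon test depending on the distribution of the variables for quantitative variables" and does not mention rescue.

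**The concern.** Of the three rescue drugs, tramadol is an opioid. Every milligram of it counts as zero in an endpoint expressed in milligrams of morphine. The undercount is not spread at random, because the rescue rule selects patients whose pain persisted despite morphine.

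Rescue is given after randomisation and is triggered by pain. The Introduction cites better analgesia and lower postoperative morphine use as effects of opioid-free anaesthesia, and Section 2.7 makes quality of analgesia an objective. If analgesia does differ between arms, rescue use may differ too. An arm that receives more tramadol would then show a lower opioid total than it really had. The direction cannot be known in advance: more tramadol in the control arm would hide a benefit of opioid-free anaesthesia, and more in the opioid-free arm would create or inflate one. At stake is whether a lower morphine total can be read as lower opioid need.

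**Working it through.** The protocol article gives no expected mean, standard deviation or rescue rate for this endpoint, so there is no stated figure to reproduce. The check has two parts: what the text fixes, and how large the effect could be.

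**1. What the text fixes**
- Unit of the endpoint: milligrams of morphine (Section 2.8).
- Rescue drugs: ketoprofen, tramadol and nefopam, alone or combined (Section 2.5.3).
- Condition for rescue: VAS above 3 despite 20 mg of morphine, by titration or cumulated over the last 4 h, plus paracetamol (Section 2.5.3).
- Rule that adds tramadol to the endpoint or to its analysis: none in Sections 2.8 or 2.9.2.

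A patient who reaches tramadol under the protocol has already had 20 mg of morphine. The recorded total is therefore not near zero. What is missing is the opioid given as tramadol on top of it.

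**2. Bias in the mean difference**

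Let r be the share of an arm that receives tramadol and u the mean uncounted morphine equivalent per such patient. Within an arm,

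mean morphine = mean total opioid − r × u.

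The morphine-only difference between arms therefore departs from the total-opioid difference by r₁u₁ − r₂u₂.
- With r₁ = r₂ and u₁ = u₂ the shift is 0, so the mean difference is unbiased.
- With equal u the shift is (r₁ − r₂) × u.
- With equal r the shift is r × (u₁ − u₂), so a difference in amount alone is enough.

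**3. Illustrative size**

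The inputs here are assumptions, not document figures and not a comment on dosing: 200 to 600 mg of tramadol per rescued patient over the 48 h window, and 10 to 20 mg of tramadol per 1 mg of morphine.

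Uncounted amount per rescued patient, u = tramadol dose / conversion ratio:

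| Tramadol | 20:1 | 10:1 |
|---|---|---|
| 200 mg | 200/20 = 10 mg | 200/10 = 20 mg |
| 600 mg | 600/20 = 30 mg | 600/10 = 60 mg |

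Shift in the mean difference, with equal u in both arms:

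| Difference in rescue use | u = 10 mg | u = 60 mg |
|---|---|---|
| 0 points | 0 mg | 0 mg |
| 10 points | 0.10 × 10 = 1 mg | 0.10 × 60 = 6 mg |
| 20 points | 0.20 × 10 = 2 mg | 0.20 × 60 = 12 mg |
| 30 points | 0.30 × 10 = 3 mg | 0.30 × 60 = 18 mg |

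These shifts apply to a comparison of means, as in the ANOVA. They do not carry over directly to a Wilcoxon test. Morphine that the patient did not need because a rescue drug worked is a separate effect and is not in the table. Ketoprofen and nefopam can produce it as well as tramadol.

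**The case against.** The strongest reply is that objective and endpoint agree: Section 2.7 asks about morphine and Section 2.8 counts morphine. That is correct. A reader might infer that the endpoint contradicts the objective, but it does not. As a measure of morphine it is sound; the problem is its use as a measure of opioid consumption.

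A reader might also infer that the patients in most pain will look as if they had been spared opioids. The rescue condition in Section 2.5.3 rules that out as a general statement, because 20 mg of morphine comes first. The text also describes the rescue drugs as complementary and nowhere says that morphine stops. These patients are undercounted on top of a substantial total. If they already rank high, a Wilcoxon comparison may change little.

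The bias is conditional. Analgesia is standardised, and Section 2.1 keeps patients and ICU staff blind to allocation. This limits differences that come from knowing the arm. It does not prevent differences that come from pain itself, since rescue responds to pain after treatment.

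Pain episodes and QoR15 are separate endpoints, so poor pain control would partly show. Neither measures opioid dose, and rescue that works could lower both pain episodes and later morphine use.

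Finally, a sensitivity analysis for a secondary endpoint may sit in the full protocol or analysis plan, neither of which is shown. Its absence from the article is therefore not the point. The point is the unit that the article does fix, which excludes an opioid the same article allows.

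**Conclusion.** The point holds in a limited form. The morphine endpoint omits an opioid that may be given once morphine and paracetamol have proved insufficient, so opioid use is undercounted in patients with uncontrolled pain. The comparison between arms, read as one of opioid use, is biased if the rate of tramadol use or the amount per rescued patient differs by arm, and not otherwise. Under the stated assumptions the mean difference moves by 1 to 6 mg for each 10 points of difference in rescue use. With no expected mean or standard deviation in the document, it cannot be said whether a shift of that size would change the conclusion on this endpoint.

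The documents do not show that rescue use will differ, nor in which direction. This is a secondary endpoint, and the main conclusion of the trial does not depend on it. A correction is still worth making because it is cheap and must be fixed before the results by arm are known.

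**What to change.** Before unblinding for the final analysis:

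1. Pre-specify total opioid consumption within 48 h of extubation, as morphine plus tramadol in morphine equivalents with one stated conversion factor. Make it either the endpoint or a named sensitivity analysis beside the morphine-only result.
2. Report the proportion of patients receiving each rescue drug by arm. Conversion of tramadol does not deal with ketoprofen and nefopam, which can also reduce morphine use.
3. Do not describe the morphine-only result as total opioid consumption.

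The cost is one derived variable and one table. A conversion factor must be chosen and will be open to argument, which is why the morphine-only result should stay visible. The sponsor must also confirm that the additional-analgesia item in the e-CRF holds the tramadol dose and not only its use. If it does not, points 2 and 3 can still be done where the drug given is recorded. The primary endpoint, the sample size and the rescue regimen need no change.
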